## Abstract

**Supplementary Information:**

The online version contains supplementary material available at 10.1186/s40359-024-01772-z.

## Background

Eating disorders (EDs) are complex mental health conditions characterized by a pathological pattern of preoccupation with weight and body shape control, inappropriate food intake, fear of gaining weight, and body image dissatisfaction [1]. While eating disorders can affect individuals of all ages, they commonly emerge during adolescence, a critical period of growth, development, and identity formation. Currently, the prevalence of adolescents with a diagnosis of ED ranges from 0.3% to 1.7% [2–4]. Due to their severity, comorbidity, and mortality risk, these disorders have serious repercussions on the physical and psychological development of children and adolescents [5, 6]. In addition, a worsening of mental health among young people has been observed as a consequence of the COVID-19 health pandemic and home confinement. This has led to an increase in the prevalence of EDs [7], as well as an aggravation of symptomatology in those already suffering from it [8, 9].

Cognitive behavioural therapy (CBT) is the most empirically supported psychological treatment for eating disorders [10, 11]. However, accessing treatment is difficult, and less than 20% of patients in need actually receive it [12]. In the adolescent population, this lack of treatment is even more noticeable [13]. In addition, its efficacy is not entirely satisfactory, as patients exhibit difficulties when it comes to recovery, such as a tendency toward chronicity, resistance to change, high level of comorbidity, and a significant percentage of relapses [14, 15]. All this reflects the existing need to work on the risk factors of eating disorders in order to minimize their occurrence.

In order to improve the prevention and treatment of EDs, the use of information and communication technologies (ICTs) has been developed in recent years. Regarding ICTs in EDs, these have been implemented in their assessment, prevention, treatment, and follow-up in various formats such as: virtual reality [16, 17], CBT via videoconferencing [18, 19], or on-line familiar therapy [20]. In terms of prevention programs, various projects have been implemented among adolescents and young people in schools. For example, the program *StudentBodies* conducts CBT online sessions in which a facilitator or guide creates group discussions about weight concerns. It consists of 8 modules of 30 min each. Different studies on its efficacy in a sample at risk of developing ED showed no significant reduction in the onset of future eating disorders [21–23]. Another example is the *eBodyProject* program. It is based on *BodyProject*, which is a program of 3 or 4 sessions guided by a clinician in which group exercises are carried out to explore the negative effects of following a thin body ideal [24]. When the program was conducted online, the acceptability was found to be better than when it was done in person [25] and studies indicate that the virtual delivery of the Body Project significantly decreased the likelihood of developing eating disorders in the future [26].

However, despite the existence of these prevention programs, there are none that are based on a mobile app. These tools have many advantages, such as accessibility anytime and anywhere, low cost, wide reach, reduced hesitation to seek assistance, and anonymity [27]. They do not require any clinician or other guide and, furthermore, young people are familiar with its use.

Regarding mobile applications for ED, different apps can be found in English, such as *Recovery Record,* focused on the self-management of typical ED behaviors and related thoughts and feelings and includes therapist feedback. Studies analyzing *Recovery Record*’s efficacy in the clinical population show that the experimental group did not obtain better results in the reduction of ED symptoms compared to the control group [28, 29]. However, the application was well received, and improved its users’ adherence and referral rates [30–32]. There is another app, called *Noom Monitor,* which is designed for self-monitoring meals, compensatory behaviors, exercise, body checking, cravings, and weight. The use of this app together with regular CBT revealed better results in two studies with adult patients with binge eating disorder and bulimia nervosa compared to patients who only received regular CBT [33, 34]. The app named *Break Binge Eating,* is based on the principles and techniques of transdiagnostic CBT for ED, and aims to normalize eating behavior, reduce the importance given to both weight and shape, and promote adaptive emotional regulation strategies. There is a study in which this app shows positive results in adult ED patients, showing a reduction in overall ED psychopathology [35]. There are other apps targeting ED, but with less empirical support, such as *TCApp* [36, 37], *FFT* [38], *FoodT* [39], or *MT—BD* [40]. All of these applications are aimed at the clinical population, but none of them focus on addressing risk factors before the disorder has developed.

In Spanish, as far as we know, there is only one mobile application designed to address core beliefs associated with eating disorders. GGED (GG Eating disorders) is a specific module developed in the GGtude platform, an app which is composed of different modules, each of them aimed at working with different mental health problems. GGtude is a commercial application, but users can access the modules under study for free. It is available for Android and iOS, and people can download it by searching for "GG OCD" in the play store or app store. The goal is to provide an easy-to-use tool to work on self-dialogues related to the core beliefs associated with psychological problems in particular. Different studies have supported the efficacy of different modules to reduce the adherence to dysfunctional beliefs associated with obsessive–compulsive disorder [41–43], or with other disorders such as dysmorphic disorder [44, 45] or emotional disorders [46]. The GGED module is composed of a total of 67 levels divided into themes like those worked on in CBT [10]. Some examples of these themes are fear of being judged, perfection of physical appearance, the need to control body weight, self-esteem, fear of food-related thoughts, physical appearance in the media, or fear of shame, among others. The GGED exercises follow the same dynamic as the rest of the modules of the GGtude mobile platform: at each level, statements are randomly presented one by one in the screen in a positive sense (e.g., "An imperfect body is a real body"), and in a negative sense (e.g., "There is nothing worse than getting fat"). (see Fig. 1). The person must identify and “accept” those beliefs that are functional, adaptive, and positive, dragging them to the lower part of the screen; and “reject” those that are dysfunctional, maladaptive, and negative dragging them to the upper part of the screen. The application notifies the user when an error occurs in accepting or rejecting a belief. Otherwise, a message appears on the screen alerting the person that they are accepting a dysfunctional sentence or rejecting a functional one. Thus, exposure to self-affirmations that challenge your maladaptive beliefs can improve your accessibility and ability to generate adaptive self-affirmations. In addition, daily coaching can help users become more aware of their internal dialogue and soften the interpretation of thoughts associated with eating disorders [47].

**Fig. 1 Fig1:**
[figure not shown]
Examples from the GGED-AD application

Preliminary efficacy data with general adult population using GGED for two weeks (3 min per day), showed a decrease in dysfunctional beliefs regarding perfectionism in physical appearance, vulnerability to weight gain, and the importance of thought control, as well as an increase in self-esteem [48].

Considering the potential of the GGED module to modify dysfunctional beliefs associated with eating disorders, as well as the fact that adolescence is a developmental stage in which individuals are vulnerable to the development of these disorders, we adapted the GGED module to the adolescent population (GGED-AD). Thus, the aim of the present study is to describe the design used to evaluate the effectiveness of GGED-AD at decreasing dysfunctional beliefs associated with eating disorders, eating symptoms, and symptoms of depression and anxiety, and increasing body satisfaction and self-esteem among adolescents through a randomized controlled trial. Following the results found in a previous study with GGtude platform for ED in adults [48], we hypothesize that after the use of the GGED-AD app for 14 days in the experimental group, there will be a decrease in the degree of ascription to dysfunctional beliefs associated with ED in adolescents at the primary level; and an increase in body satisfaction and self-esteem and decrease in eating symptomatology at the secondary level. It is also hypothesized that there will be no change in emotional symptoms, as has been found in previous research on the GGED module in the adult population [48], or in this variable with the GGOC module [42, 43]. Results are also expected to be maintained in the subsequent follow-up a month after the use of the app.

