### Sample

The study will include adolescents between the ages of 13 and 16 from an educational center in the Valencian Community.

The inclusion criteria will include (1) ages between 13 and 16, (2) informed consent form signed by both parents or guardians and the adolescents, and (3) access to a smartphone with Internet connectivity.

The sample size was calculated using the free program G*Power (version 3.1.9.7) [50]. To determine the size of the effect of the predictor variables on the response, Cohen’s conventional tables will be used. It was determined that a sample of at least 68 participants achieve a power of a power of 0.805 at alpha = 0.05 and a medium effect size of effect (*f* = 0.15).

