#### Secondary outcomes

*Eating Disorder Examination Questionnaire* (*EDE-Q*; Fairburn & Cooper, 1993 [54]; Spanish version: Peláez-Fernández et al., 2012 [55]). It is a 36-item self-report questionnaire that assesses the range, frequency and severity of behaviors associated with a diagnosis of an eating disorder. It comprises four subscales (restriction, food concern, weight concern and figure concern) which are composed of attitudinal and behavioral items. For the present study, we will only use 22 attitudinal items. Items are scored on a 7-point Likert-type scale, ranging from 0 (“No day/ No time/ Not at all”) to 6 (“Every day/ Always/ Completely”). Its original version and its validation in Spanish present an adequate internal consistency (Cronbach's α is 0.86, 0.75, 0.93 and 0.74 for the four scales).

*Body Appreciation Scale-2 (BAS-2;* Tylka & Wood-Barcalow, 2015 [56]; Spanish version: Swami et al., 2017 [57]). It is a single-factor questionnaire that evaluates body satisfaction with 10 items on a 5-point Likert scale (from 1 = “Never” to 5 = “Always”). Both its original and Spanish versions present high internal consistency with Cronbach's α above 0.90.

*The Patient Health Questionnaire (PHQ-4;* Kroenke et al., 2009 [58]; Spanish version: Lenz & Li, 2022 [59]). This is a 4-item measure of two factors: depression and anxiety. It assesses the symptoms experienced by participants during the 2-week period before taking the survey (two items are used for the main symptoms of anxiety and two for depression). The response format is a 4-point Likert-type scale (from 0 = “Never” to 3 = “Almost every day”), and its validation presents adequate psychometric qualities, with an internal consistency (Cronbach's α) of 0.86 (depression) and 0.91 (anxiety).

The *Single-Item Self-Esteem Scale (SISE*; Robins et al., 2001 [60]) is a self-report measure in which the person has to indicate how the statement “I have high self-esteem” describes him/her on a 9-point scale (from 1 = "Not very true for me" to 9 = "Very true for me"). This scale presents high test–retest reliability and a similar criterion validity coefficient with the Rosenberg Self-Esteem Scale (Rosenberg, 1965 [61]) above 0.80.

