## Discussion

### Expected outcomes

With respect to the primary outcomes, a decrease in the degree of ascription to dysfunctional beliefs associated with eating disorders is expected in the experimental group at the T2 assessment. These changes are also expected to be maintained in the follow-up evaluation (T3) in this group. No changes are expected in the control group. The cognitive training on the adaptive and maladaptive beliefs related to ED is the principal objective of the app. Therefore, a reduction in ED dysfunctional beliefs is expected in the participants of the experimental group after the use of the GGED module, given that in other studies conducted with different modules of the GGtude platform this change was also found in the thoughts worked on (e.g., obsessive-compulsive disorder [41–43], body image [44, 45, 65], anxiety [47, 66, 67], emotional disorders [46, 68], and self-esteem [69]). Moreover, the preliminary efficacy data of GGED used in the adult population also found these changes at post-intervention [48]. It is expected that those results will be replicated in adolescents.

Regarding secondary outcomes, an increase in body satisfaction and self-esteem, and a decrease in eating symptomatology are expected in the experimental group at T2. Their maintenance is also expected at T3. None of them are expected in the control group. Changes in self-esteem and in diverse symptomatology have been found in other studies with other modules, such as obsessive–compulsive disorder [41–43] or emotional disorders [46]. With respect to body satisfaction, there are positive results [44, 45] with another module of the GGtude platform targeting body image concerns in young people (between 20 and 30 years of age). Some maladaptive beliefs worked on in this module (e.g., inflated importance of one’s appearance, perceiving the body as an object, and appearance related perfectionism) are also included in the GGED-AD module. In the same way, these results are also expected in the present study which is aimed at ED in the adolescent population. As for emotional symptomatology, no changes are expected, given that the studies with other modules have not found changes [42, 42, 48], or these were not maintained over time [65].

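### The no-change hypothesis for emotional symptoms sits in tension with the stated aim, and the design as described cannot confirm it

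*Protocol article*

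**What the plan says.** The last paragraph of the Background, in the Protocol article, gives the aim as describing the design used to "evaluate the effectiveness of GGED-AD at decreasing dysfunctional beliefs associated with eating disorders, eating symptoms, and symptoms of depression and anxiety", together with increasing body satisfaction and self-esteem. The same paragraph then sets out the hypotheses. Improvement is predicted for dysfunctional beliefs, eating symptoms, body satisfaction and self-esteem. For mood the prediction is different: "It is also hypothesized that there will be no change in emotional symptoms", on the ground that earlier work with the adult module and a related module found none. Expected outcomes, in the Discussion, repeats this: "As for emotional symptomatology, no changes are expected".

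The instrument is the PHQ-4, listed under Secondary outcomes: "This is a 4-item measure of two factors: depression and anxiety". Statistical analysis names mixed models for repeated measures for the response variables, with group, gender and time as factors and baseline scores as covariates. It gives no separate rule for the PHQ-4 and no equivalence margin. Sample asks for "a sample of at least 68 participants", with power "0.805 at alpha = 0.05" for an effect size of 0.15.

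**The concern.** There are two linked problems. First, depression and anxiety share the word decreasing with outcomes for which a decrease is predicted, yet their own prediction is no change. A reader cannot tell whether a fall in PHQ-4 would count as success or as a failed prediction.

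Second, no change is put forward formally, as a hypothesis alongside the efficacy hypotheses. Supporting it would need evidence that any effect is small, which means an interval judged against a margin. A model that tests for a difference, in a sample sized to find one, does not supply this. Failing to reject the null is not evidence that the null is true.

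At stake is what the trial may conclude about mood in 13- to 16-year-olds. A modest benefit or a modest worsening would probably be non-significant, and the present wording leaves room to report it as the predicted absence of change.

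**Working it through.** **Inputs from the article.** Total sample at least 68; alpha 0.05; power 0.805; effect size 0.15 (Sample). Two arms (Study design). Mixed model with baseline covariate (Statistical analysis).

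**Assumptions, because the article gives no figure.** Allocation 1:1, so 34 per arm. The hypothesis is read as a between-group difference at one time point, adjusted for baseline. Correlation r between baseline and follow-up runs from 0 to 0.7. True effects and margins are in SD units. No dropout; the article gives no rate.

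**1. The plan's own figure.** If 0.15 is read as f-squared in a regression with two predictors, the noncentral F has λ = 0.15 × 68 = 10.2 with 2 and 65 degrees of freedom. Power is 0.804 and the smallest sample reaching 80% is 68, which matches the stated 68 and 0.805 to within 0.001. If 0.15 is read literally as f in a 2-group by 3-time interaction with correlation 0.5, power at 68 is 0.769 and 74 would be needed. On either reading this is power to detect an effect. Nothing in it concerns showing that an effect is absent.

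**2. Standard error.** SE = √((1 − r²) × 2/34).
- r = 0: √0.0588 = 0.243 SD
- r = 0.5: √(0.75 × 0.0588) = 0.210 SD
- r = 0.7: √(0.51 × 0.0588) = 0.173 SD

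**3. Precision, missed effects and equivalence power.** The 95% half-width is 1.997 × SE (t with 66 degrees of freedom). The probability that a true effect d is non-significant is 1 − Φ(d/SE − 1.96), ignoring the negligible opposite tail. Equivalence power, for two one-sided 5% tests with true difference 0 and margin M, is 2Φ(M/SE − 1.645) − 1, floored at 0.

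| r | 95% half-width (SD) | Non-significant if d = 0.3 | Equivalence power, ±0.3 SD | Equivalence power, ±0.5 SD |
|---|---|---|---|---|
| 0 | 0.48 | 77% | 0 | 32% |
| 0.5 | 0.42 | 70% | 0 | 54% |
| 0.7 | 0.35 | 59% | 7% | 79% |

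Examples:
- r = 0, d = 0.3: 0.3/0.243 − 1.96 = −0.72, so power is 0.235 and the miss rate 0.765.
- r = 0.7, M = 0.5: 0.5/0.173 − 1.645 = 1.24, so power is 2 × 0.893 − 1 = 0.79.

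**4. Sample that equivalence would need.** For 80% power, n per arm = 2(1 − r²)((1.645 + 1.282)/M)². In total this is 382 (r = 0) to 196 (r = 0.7) for ±0.3 SD, and 138 to 70 for ±0.5 SD.

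**The case against.** The strongest reply has four parts.

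- **Scope versus prediction.** The aim lists what will be evaluated and the hypotheses say what is expected. A trial may evaluate an outcome and predict no effect on it, and the prediction is the same in Background and Discussion. This stands as far as it goes: a reader might infer an outright contradiction, and the text supports only a tension. It does not remove the shared directional wording.
- **No decision rule is stated.** A reader might infer that a non-significant PHQ-4 result will be counted as confirmation. The article nowhere says so, and a margin or interpretation rule for a secondary outcome could sit in an analysis plan that is not shown. This also stands. But a margin added elsewhere would leave the published aim and hypothesis unreconciled, and at 68 participants only a wide margin with a high baseline correlation comes near adequate power.
- **The hypothesis can fail.** It is tempting to say that any PHQ-4 result fits one statement or the other. That is not so: a detected worsening fits neither, and a detected improvement refutes the hypothesis.
- **The figures rest on outside inputs.** The allocation ratio, correlation, margins and true effect are assumed, 68 is a minimum, and the planned model uses repeated measures instead of one contrast. That is fair, and it is why ranges are given. Equivalence power at ±0.3 SD, for example, is near zero but not exactly zero across the range.

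**Conclusion.** The point holds in this form: the aim and the hypothesis for emotional symptoms need reconciling, and the article states a null hypothesis that the design it describes cannot confirm. With 34 per arm and r between 0 and 0.7, a single-time contrast leaves effects of roughly a third to a half of an SD inside a 95% interval centred on zero. It would more often than not miss a true effect of 0.3 SD. The nearest approach to an adequate equivalence test is 79% power, which needs ±0.5 SD, r = 0.7 and no dropout, while Challenges allows that dropout may exceed expectation. A sample above the minimum would narrow the intervals.

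The PHQ-4 is a secondary outcome, so the primary outcome, the sample size and the choice of model are untouched. It is still worth correcting, because it bears on what may be concluded about mood in adolescents and costs almost nothing.

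**What to change.** 1. In the Background and in Expected outcomes, present no change in emotional symptoms as a prior expectation from earlier studies, not as a hypothesis to be confirmed.
2. Report PHQ-4 depression and anxiety as two-sided secondary outcomes, each with estimate and 95% confidence interval.
3. State that a non-significant result will not be taken to show absence of effect, whether benefit or worsening.
4. Align the aim with this, for example by listing depression and anxiety separately as outcomes whose change in either direction will be estimated.

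This changes wording and a reporting rule only, with no extra participants, visits or modelling. The price is a weaker claim about emotional symptoms. If the team wants to claim absence of effect, it would instead have to fix a margin beforehand and require the 90% interval to lie inside it, with the sample sizes shown in step 4 of the working.

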## Methods

The present protocol complies with the Standard Protocol Items: Recommendations for Interventional Trials (SPIRIT) checklist [49]. Additional file shows this in more detail (see Additional file 1).

### Sample

The study will include adolescents between the ages of 13 and 16 from an educational center in the Valencian Community.

The inclusion criteria will include (1) ages between 13 and 16, (2) informed consent form signed by both parents or guardians and the adolescents, and (3) access to a smartphone with Internet connectivity.

The sample size was calculated using the free program G*Power (version 3.1.9.7) [50]. To determine the size of the effect of the predictor variables on the response, Cohen’s conventional tables will be used. It was determined that a sample of at least 68 participants achieve a power of a power of 0.805 at alpha = 0.05 and a medium effect size of effect (*f* = 0.15).

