### Statistical analysis

Statistical analyses will be performed using the free software R. To avoid overly optimistic estimates of the efficacy of the experiment, an intention to treat (ITT) approach will be used, using the method of the multivariate imputation by chained equations algorithm (MICE) [64].

Descriptive statistics will be used to report means, standard deviations and frequencies. In addition, tests will be performed to evaluate differences between the different variables considered in the study. To predict the different response variables under study, mixed models for repeated measures (MMRM) will be used, in which the outcomes measures are dependant variables, and the independent variables are group of the study (experimental or control), gender (male/female/other) and time (T1, T2, and T3). In addition, the baseline scores for each of the factors evaluated will be used as covariates to control that the T1 scores do not affect the results of the efficacy of the app.

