### Challenges

Some challenges that may be encountered when carrying out the study are: (1) making a schedule that interrupts the lessons as little as possible; (2) that the participants use the application properly, in silence and focused while reading the sentences; (3) that participants complete the app during weekends. In order to overcome these challenges, the researchers will meet with the team of teachers to agree on a procedure that will cause as little disruption as possible to their work. In addition, the researchers will be there every day to accompany the adolescents as they complete the app, to remind them of the importance of completing the app seriously, to see that they do not answer randomly and to encourage them to complete the app over the weekend. It is possible that the number of dropouts will be higher than expected. Thus, the goal is to motivate participants as much as possible to minimize the dropout rate.

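### The sample-size sentence calls f = 0.15 a medium effect, which fits f² and not f, and its power of 0.805 is not shown to apply to the planned group comparison

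*Protocol article*

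**What the plan says.** The Sample section of the protocol article gives the whole justification of the sample size. It names G*Power 3.1.9.7 and introduces the effect size with "To determine the size of the effect of the predictor variables on the response, Cohen’s conventional tables will be used". It then concludes that "a sample of at least 68 participants achieve a power of a power of 0.805 at alpha = 0.05" and describes the assumed effect as "a medium effect size of effect (*f* = 0.15". It does not name the test family, the number of predictors or degrees of freedom, the tested effect, any correlation between measurements or any expected loss.

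The Statistical analysis section says that "mixed models for repeated measures (MMRM) will be used", with study group, gender (three categories) and time (T1, T2, T3) as independent variables and baseline scores as covariates. The Background and Expected outcomes sections pose the primary question: dysfunctional beliefs, measured by the EDBQ, should fall in the experimental group at T2 and not in the control group, and the change should last to T3.

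**The concern.** Two things do not fit. First, the effect size conflicts with the convention that the sentence invokes. In Cohen's conventions the medium value is 0.15 for f² in multiple regression and 0.25 for f. Calling f = 0.15 medium therefore has either the wrong symbol or the wrong adjective. The choice matters: f = 0.15 is f² = 0.0225, less than a sixth of 0.15.

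Second, the phrase about predictor variables and a response suggests a regression test, whereas the trial's question is whether the experimental group differs from control in EDBQ after the intervention, estimated from a repeated-measures model adjusted for baseline. Power for a joint test of several predictors, or for a test whose correlation assumption is not given, does not carry over to that difference.

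At stake is how a null result would be read. On the printed sentence, a reader would take it as evidence against a medium effect from a trial with about 80% power, which the document does not establish.

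**Working it through.** **Inputs from the article.** N = 68, power 0.805, alpha 0.05, effect 0.15 labelled f and called medium (Sample); two arms (Study design); group, gender, three time points and baseline covariates (Statistical analysis).

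**Assumptions, not in the article.** 1:1 allocation (34 per arm), two-sided testing for the group contrast, and a baseline–T2 correlation r shown from 0 to 0.8.

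**Step 1: reproduce the stated figure.** For a fixed-model regression F test, λ = f²·N with df (u, N − u − 1). With f² = 0.15, u = 2, N = 68:

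- λ = 0.15 × 68 = 10.2, df (2, 65), power **0.8044**.
- At N = 67 the power is 0.798, so 68 is exactly the minimum for 0.80.

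This agrees with the printed figure to within 0.001, although 0.8044 rounds to 0.804. Testing 2 of 3 to 8 predictors also gives N = 68, with power 0.804 to 0.802.

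**Step 2: take the printed symbol literally.** With f = 0.15, f² = 0.0225 and λ = 0.0225 × 68 = 1.53. Power is 0.17 in the same 2-df regression and 0.23 in a two-group comparison.

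**Step 3: look for another route to 0.805.** For a group-by-time interaction with 2 groups and m = 3 times, λ = f²·N·m/(1 − ρ) with df (2, 132). With f = 0.15, f²·N·m = 0.0225 × 68 × 3 = 4.59:

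| ρ | λ | Power |
|---|---|---|
| 0.50 | 9.18 | 0.77 (0.80 needs N = 74) |
| 0.54 | 9.98 | 0.805 |
| 0.60 | 11.48 | 0.86 |

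So a repeated-measures calculation can also give 0.805, but only with an unstated correlation of about 0.54. On that route the symbol is right and the word medium is wrong.

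**Step 4: power for the group difference at T2.** For two equal groups d = 2f. With n = 34 per arm, the noncentrality is d/√(1 − r²) × √(n/2), with 66 df unadjusted and 65 df adjusted. For example, d = 0.5 at r = 0.6 gives 0.5/0.8 × √17 = 2.58 and power 0.72.

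| Reading of the effect | r = 0 | r = 0.6 | r = 0.7 | r = 0.8 |
|---|---|---|---|---|
| f² = 0.15 as the group effect, d = 2√0.15 = 0.77 | 0.88 | 0.98 | 0.99 | above 0.99 |
| Medium f = 0.25, d = 0.50 | 0.53 | 0.72 | 0.81 | 0.92 |
| Literal f = 0.15, d = 0.30 | 0.23 | 0.33 | 0.40 | 0.53 |

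In the first row, 0.88 is the figure to use if f² = 0.15 already describes the adjusted effect. The higher values apply if d = 0.77 is measured against the unadjusted SD.

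**Step 5: detectable effect at 80% power, 34 per arm.** Unadjusted, d = 0.69. At r = 0.6, 0.69 × √(1 − 0.36) = 0.69 × 0.8 = 0.55.

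**The case against.** **The source of 0.805 is not documented.** This stands. A reader might infer that the figure was computed for a two-predictor cross-sectional regression. The wording on predictors, the conventional value 0.15 and the exact minimum at N = 68 make a 2-df regression test the likeliest source, but the article names no test, and the interaction in Step 3 reproduces the printed figure too.

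**The trial may have the power it claims.** This also stands. A reader might infer that the group comparison lacks 80% power. The documents do not support that: power is 0.88 if f² = 0.15 is the 1-df group effect, and 0.81 for d = 0.5 if the baseline correlation is 0.7. The 0.88 case does not rescue the sentence, however. A d of about 0.77 is close to the conventional large value of 0.8, and the article prints 0.805, not 0.88.

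**The T2 contrast is not fixed as the single primary test.** The planned model has three times, and a group-by-time test would have 2 df. That is fair, and it is one more reason to name the tested effect. T2 is used here because the expected outcomes place the primary change there.

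**An article may leave detail to the full protocol.** That excuses a missing test family or correlation. It does not excuse a printed effect size that contradicts the convention it cites.

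**Dropout.** The Challenges section concedes "It is possible that the number of dropouts will be higher than expected", and the Sample section states no allowance. This is only supporting: 68 is given as a minimum, imputation is planned, and the expected rate may stand elsewhere.

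**Conclusion.** The sentence is wrong as written: under the conventions it invokes, f = 0.15 is not medium. The stated power of 0.805 is also not shown to apply to the experimental-versus-control difference in EDBQ at T2 from the planned model. Whichever source is right, part of the sentence must change: the symbol if it was f² = 0.15, the word medium if it was f = 0.15.

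The size of the problem depends on the effect meant. At a conventional medium d = 0.5, power reaches about 0.80 only if the baseline correlation is about 0.7 or more, and it is 0.53 without adjustment. At the printed f = 0.15 it stays at or below 0.53 for correlations up to 0.8. At f² = 0.15 taken as the group effect it exceeds the claim. Power for the planned comparison is therefore not established, which is different from being shown inadequate. These figures rest on 34 analysed per arm, a two-sided 0.05 test at one time point, and correlations that the article does not give.

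**What to change.** In the Sample section, correct the effect-size symbol or the adjective, and name the G*Power test, the tested effect and its degrees of freedom. Replace the 0.805 sentence with the power or detectable effect for the group contrast in EDBQ, together with the assumed baseline correlation and expected loss. Possible wording: *68 analysed participants (34 per arm) give 80% power at two-sided 0.05 for a group difference at T2 of d = 0.69 unadjusted, or about 0.55 if the baseline–T2 correlation is 0.6.*

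If loss is expected, add the matching figures. As an illustration only, 20% loss (27 per arm) would make these 0.78 and 0.62; the rate is an assumption, and the sponsor should use its own.

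The cost is a change of wording in the protocol and, if one exists, the statistical analysis plan. N, design and conduct stay as they are. The drawback is that the stated figure will probably look less favourable.
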